Currently, UF recommend by most of the guidelines are usually considered for patients with refractory congestion not responding to medical therapy. Previous research found although UF improve hemodynamics in acute decompensated HF refractory to standard medical therapy, it was also associated with high incidence of renal function damage and high in-hospital mortality [6]. However, other research found UF within 12 h of hospitalization in HF patients with volume overload and LD resistance before IV LDs effectively decreased length of stay and readmissions up to 3 months without change of renal function [7]. At present, most of the studies support UF should be considered as early treatment strategies (24 h after admission) in patients with severe HF instead of a “rescue therapy”. Early UF may prevent undesirable cardiorenal syndrome and sodium-volume overload before renal tubular damage induced by further neurohormonal activation and side effects caused by high dose LDs [8, 9].

Taken together, previous related studies showed UF is more effective in decongestion, haemodynamic variables and clinical outcome improvement, as well as restoring LD responsiveness compared with LDs. But most of the studies were based on the foreign population and did not define the exact time period from admission to UF. We do not have the related data for early UF in Chinese population. Furthermore, former study did not define how to screen out the patients recommended for early UF by specific scoring system. Our study aims to determine if early UF 24 h within admission in acute HF is superior to IV LDs in clinical parameter improvement without adverse events and prevents rehospitalization up to 30 days in Chinese population.

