### Study outcomes

The primary end points of EUC-CHF are the changes of weight loss and dyspnea severity score at every scheduled visit which are considered as the part of a single composite endpoint, as well as the occurrence of clinically major bleeding defined by TIMI or GUSTO criteria [12].

Secondary outcomes include: net fluid loss, length of stay in CCU or ICU, change of score by MLWHFQ functional capacity, change of serum and ultrafiltrate concentrations of endotoxin, ET-1, TNF-a, IL-6 and IL-10, changes of cardiac function (the NYHA classification), changes in N-terminal proB-type natriuretic peptide (NT-proBNP) level, changes of LDs dose, HF rehospitalizations for congestive HF in 30 days after discharge, cardiovascular death and all-cause death in 30 days after discharge, change of blood pressure, changes in hepatic and renal function (serum creatinine concentration, estimated glomerular filtration rate [eGFR]), serum electrolytes, hemoglobin and incidence of acute coronary syndrome at scheduled visits.

Weights will be obtained at every scheduled visit using the same balance with the patient shoeless in a hospital gown after emptying the bladder. Weight loss is the difference between weight at baseline and the weight recorded at subsequent visits.

The dyspnea severity score by a proposal to standardize dyspnea measurement in clinical trials of acute heart failure syndromes by International Working Group on acute heart failure of European Society of Cardiology is used for the assessment of dyspnea [13].

Total fluid intake and output (ultrafiltrate and urine) measured at every scheduled visit after enrollment will be used to calculate net fluid losses.

Glomerular filtration rate will be calculated according to the abbreviated Modification of Diet in Renal Disease (MDRD) equation [14].

Acute coronary syndrome includes unstable angina, ST segment elevated myocardial infarction and non-ST segment elevated myocardial infarction. Myocardial infarction is defined according to the fourth universal definition of myocardial infarction [15]. Death will be considered cardiac according to the 2014 ACC/AHA key data elements and definitions for cardiovascular endpoint events in clinical trials [16].

We also will collect all the urine output after patients are enrolled to receive standard medical therapy or early UF until 72 h after the end of study treatment. Then we will measure the average urine electrolytes for every enrolled patient.

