The ability to predict the therapeutic effect of UF by patients’ individual characteristics as well as systolic blood pressure, heart rate, severity of edema, renal and hepatic function, NYHA classification, left ventricular ejection fraction, chamber diameter, concomitant disease and medication;The influence of different patients’ individual characteristics including gender, age, height and weight on the effect of UF for fluid removal and alleviation of dyspnea;The influence of baseline systolic blood pressure and heart rate on the effect of UF for fluid removal and alleviation of dyspnea;The influence of baseline severity of edema (i.e., edema of lower extremity and congestion of other organs) on the effect of UF for fluid removal and alleviation of dyspnea;The influence of baseline renal and hepatic function on the effect of UF for fluid removal and alleviation of dyspnea;The influence of different baseline cardiac function (including NYHA classification and left ventricular ejection fraction) on the effect of UF for fluid removal and alleviation of dyspnea;The influence of different baseline chamber diameter on the effect of UF for fluid removal and alleviation of dyspnea;The influence of different baseline concomitant disease on the effect of UF for fluid removal and alleviation of dyspnea;The influence of different concomitant medication on the effect of UF for fluid removal and alleviation of dyspnea;

Subgroup analysis of primary efficacy endpoint will be estimated using a stratified Cox model. The subgroup analysis will be tested by chi-square or Fisher’s exact tests.

The primary safety endpoints and secondary endpoints will be presented by summary statistics, as number of patients, event counts and percentage, variable counts and percentage.

All comparisons will report *p* values on the basis of 2-sided tests, and a p value ≤ 0.05 will be considered statistically significant. All statistical analyses will be performed using SPSS Statistics version 22 software.

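### A blanket p ≤ 0.05 rule conflicts with the descriptive plan for secondary outcomes, and the superiority aim draws on those outcomes, so their inferential status is unsettled

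*Protocol article*

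**What the plan says.** In the protocol article, Statistical analysis, two adjacent statements govern the secondary outcomes. The first is descriptive: "The primary safety endpoints and secondary endpoints will be presented by summary statistics, as number of patients, event counts and percentage, variable counts and percentage". The second sets a rule for everything: "All comparisons will report *p* values on the basis of 2-sided tests, and a p value ≤ 0.05 will be considered statistically significant". No test, model or time point is named for any secondary outcome. The efficacy analysis that is specified in full is the log-rank and Cox analysis of the primary efficacy endpoint.

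The last paragraph of Background gives the aim as finding out whether early UF is "superior to IV LDs in clinical parameter improvement without adverse events and prevents rehospitalization up to 30 days in Chinese population". The Discussion part of the Abstract says nearly the same. Rehospitalization is not a primary endpoint; under Study outcomes it stands among the secondaries. That list opens "Secondary outcomes include: net fluid loss, length of stay in CCU or ICU, change of score by MLWHFQ functional capacity" and runs on through inflammatory mediators, cardiac function, deaths, blood pressure and laboratory values. It is not ranked, and no item is marked as key or exploratory.

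**The concern.** The two sentences give different answers to a basic question: may a secondary outcome be declared statistically significant? The answer matters because the aim reaches beyond the primary endpoint. One component, 30-day rehospitalization, is a secondary outcome. The other, improvement in clinical parameters, names no parameter, so NT-proBNP, NYHA class, net fluid loss or creatinine could each be offered as meeting it.

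- If the blanket rule covers secondaries, a favourable p value on any of them could be reported as significant support for superiority even when the primary comparison fails. Nothing in the article prevents this.
- If the descriptive sentence governs, the rehospitalization part of the aim has no analysis that could answer it.

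Either way the aim and the analysis do not match.

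**Working it through.** The article states no familywise error rate and no number of comparisons, so there is no figure of its own to reproduce.

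**Step 1. Count the secondaries that can be compared between arms** (Study outcomes), each taken once:

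- Net fluid loss, CCU/ICU stay, MLWHFQ score: 3.
- "change of serum and ultrafiltrate concentrations of endotoxin, ET-1, TNF-a, IL-6 and IL-10": 5 serum markers. Ultrafiltrate values are left out because the control group has none.
- NYHA class, then NT-proBNP "level, changes of LDs dose, HF rehospitalizations for congestive HF in 30 days after discharge": 4 (NYHA, NT-proBNP, diuretic dose, HF rehospitalization).
- "cardiovascular death and all-cause death in 30 days after discharge, change of blood pressure": 3.
- Hepatic function, creatinine, eGFR, then "serum electrolytes, hemoglobin and incidence of acute coronary syndrome at scheduled visits": 6.

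Total: 3 + 5 + 4 + 3 + 6 = 21, of which 17 are continuous or ordinal and 4 are binary (HF rehospitalization, cardiovascular death, all-cause death, acute coronary syndrome).

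**Step 2. Reading A: secondaries may be tested.** Take one two-sided 0.05 test per variable, with no true effect on any of them.

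- Independent, either direction: 1 − 0.95^21 = 0.659.
- Independent, favouring UF: 1 − 0.975^21 = 0.412.
- Expected number of false positives: 21 × 0.05 = 1.05.

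The outcomes are correlated, but the article gives no correlations. Simulation of equicorrelated normal statistics (400,000 draws), at assumed common correlations, gives:

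| Correlation | Either direction | Favouring UF |
|---|---|---|
| 0.3 | 0.555 | 0.289 |
| 0.5 | 0.430 | 0.216 |
| 0.7 | 0.295 | 0.147 |

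Against the nominal 0.025 in UF's favour, the range runs from 0.147/0.025 = 5.9 times to 0.412/0.025 = 16.5 times.

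**Step 3. Allow for rare binary outcomes.** At 20 v 20, Fisher's exact test has a true two-sided size of about 0.00005, 0.002, 0.012 and 0.023 at assumed event rates of 2%, 5%, 10% and 20%. Take 17 tests at full size and 4 binary tests at assumed rates of 20% (rehospitalization), 5% and 5% (the two deaths) and 2% (acute coronary syndrome), all independent:

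- Either direction: 1 − 0.95^17 × (1 − 0.0226) × (1 − 0.0019)² × (1 − 0.00005) = 0.593.
- Favouring UF, by the same method with one-directional sizes: 0.358.

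So the 21-test figures in step 2 are slightly high. In the other direction, the article schedules six follow-up visits (end of treatment; 24, 48 and 72 h later; discharge; 30 days after discharge), and testing at each would raise the figures.

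**Step 4. Reading B: secondaries are descriptive only.** There are then no secondary tests and no inflation, but the rehospitalization aim is left with counts and percentages. Even if it were tested, the bar would be high. With no events in one arm of 20:

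- 4 v 0: p = 2 × C(20,4)/C(40,4) = 2 × 4,845/91,390 = 0.106.
- 5 v 0: p = 2 × C(20,5)/C(40,5) = 2 × 15,504/658,008 = 0.047.

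**The case against.** The strongest reply is that the article already makes secondaries descriptive. That sentence comes immediately before the blanket rule, and the rule can be read as covering only the comparisons specified elsewhere: baseline, primary efficacy and subgroups. On this view no secondary test exists, and ordering or multiplicity rules belong in an analysis plan that is not shown.

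Part of this stands. A reader might infer that the plan sets out 21 tests at 0.05; it does not, and the absence of a hierarchy would not by itself be a finding. But the rule as published says all comparisons, the section opens by promising to compare the two groups, and the aim asks a comparative question about rehospitalization. The problem is a stated rule that conflicts with its neighbour and with the aim. A separate analysis plan could settle it only by overriding one of the published statements.

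Two further objections bear on size. First, several of the 21 mainly track safety. Restricting the count to net fluid loss, CCU/ICU stay, MLWHFQ, NYHA, NT-proBNP and diuretic dose gives 1 − 0.975^6 = 0.14 favouring UF under independence. Second, independence is not credible: eGFR is calculated from creatinine by the MDRD equation, and cardiovascular deaths are a subset of all deaths. Both are fair, and they are why a range is given. A global null is also doubtful for diuretic dose, because IV loop diuretics are stopped during UF.

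**Conclusion.** The concern holds as an unresolved conflict between two adjacent sentences, made consequential by an aim that includes a secondary outcome and an unnamed set of clinical parameters. If testing is permitted, the chance of at least one false secondary result favouring UF is about 0.41 under independence and 0.15 to 0.29 at assumed correlations of 0.7 to 0.3. In either direction the figures are 0.66 and about 0.30 to 0.56. All assume 21 variables, one test each and no true effects, and they fall somewhat when Fisher's conservatism is counted. If testing is not permitted, part of the stated aim goes unanswered.

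Three stronger readings are tempting but unsupported:

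- That the aim rests on the secondaries. It also draws on weight loss and dyspnea, the primary efficacy endpoint, which has its own log-rank test.
- That a chance win for UF is likely. The 0.66 counts both directions under independence; in UF's favour the chance is substantial but below one half.
- That an isolated secondary p ≤ 0.05 would more probably be noise than effect. The article gives no power, effect size or prior basis for that statement.

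**What to change.** In Statistical analysis, state that the p ≤ 0.05 rule does not apply to secondary outcomes; that these are exploratory; and that they are reported as between-arm differences with 95% CIs and no claim of significance. This leaves the rule for other comparisons as it is.

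In the Abstract and Background, tie superiority to the primary efficacy endpoint and describe rehospitalization and the other parameters as exploratory. If the sponsor wants to keep the rehospitalization claim, name 30-day HF rehospitalization as the single key secondary and test it at 0.05 only if the primary efficacy test is significant, accepting how much separation 20 per arm would require.

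The change needs a few sentences and no extra patients or data. Its downside is that isolated secondary p values can no longer be called significant.

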## Discussion

In the EUC-CHF study, we investigate whether early UF (with 24 h after admission) in patients hospitalized for HF worsening and significant fluid overload could help to relieve volume overload and symptom, as well as decrease short-term recurrence of acute HF and rehospitalization.

So far most of the previous researches focused on the benefits of UF in population with LD resistance. A retrospective cohort study from Asian population found UF in patients with decompensated HF and LD resistance achieved lower urine output, greater fluid loss, greater weight loss and a shorter duration of hospitalization than the standard care group. At 90 days, the UF group had fewer emergency department visits and rehospitalizations for HF [17]. In patients with acute decompensated HF due to fluid overload who whether or not have LD resistance, it is unclear about the appropriate time required to start UF. Previous randomized controlled trials (RAPID-CHF, UNLOAD, CUORE and AVOID-HF trials) compared UF to usual care with IV LDs in hospitalized patients with congestion and decompensated HF. Some of the enrolled patients received UF within the first 24 h of admission. The results from these trials all indicated that early UF safely and effectively reduced congestion, decreased length of stay, HF rehospitalizations, and cardiovascular events in acute HF patients. Clinical benefits of early UF in some of these trials last for 3 months to 1 year [4, 8, 18, 19]. Renal function changes were similar between UF and IV LDs in all of these trials. Two studies in acute renal failure after cardiac surgery demonstrated that early recognition of acute renal failure and initiating UF at early-stage are of vital importance. Early UF reduced in-hospital mortality in postcardiac surgery patients with acute renal failure [20, 21]. However, when UF was initiated late during hospitalization, particularly in patients who had already developed acute kidney injury, as in the CARRESS-HF trial, UF may lose its advantage over pharmacologic therapy. This indicated that UF should be considered as an early strategy rather than a rescue treatment. UF stated late when patients developed hemodynamic deterioration may be of less benefit and associated with a higher rate of adverse events such as renal dysfunction [22]. So we will enroll patients with acute decompensated HF due to fluid overload within 24 h after admission.

Currently, clinical UF use differs greatly among different centers, countries and physicians due to widely accepted consensus or guidelines. Bagshaw SM et al. proposed an algorithm aimed to evaluate when to initiate RRT. The algorithm included some patient-related factors, which may influence the time point of initiating RRT [23]. Equally, a clinical scoring system that is based on the patient’s clinical and laboratory information on admission as well as other potential risk factors obtained from present available trials may be useful for screening out patients suitable for UF. Using this system probably contribute to avoid unnecessary risks of UF. Amir Kazory et al. suggested a number of potential factors such as the primary renal structural disease, age, ejection fraction, blood pressure, serum sodium level, BNP level, presence of right-sided HF, history of LD resistance in previous hospitalizations, and progression of congestion despite high-dose LDs may be used as predictors for the responders from UF [24]. So our study will record baseline characteristics for subgroup analysis. We expect to find the risk factors associated with the non-responsiveness to UF. Also, we try to seek out certain patient-based clinical and laboratory parameters that could help to screen out patients appropriate for early UF.

Although experts and previous evidence from several randomized trials support the view that early UF resulted in more body fluid depletion, the timing of UF in acute HF patients in most trials are not considered as a risk factor [25]. It is not certain when and for which population is suitable to start UF. Further studies are needed to determine the clinical significance of timing for UF. So far there is no such research in China. In the present study, we will analyze the efficacy of early UF (within 24 h after admission) versus conventional pharmacologic therapy in Chinese patients with severe decompensated HF who are hospitalized for HF worsening and overt fluid overload. Thereafter, we hope to establish a scoring system based on Chinese population with acute decompensated HF to screen out appropriate candidates for early UF with the purpose of achieving better volume depletion and clinical outcome improvement. The scoring system may consist of the timing of UF as well as certain patient-based clinical and laboratory parameters.

Additionally, patients with edema due to acute HF had higher concentrations of endotoxin and cytokines [26–28]. Bacterial or endotoxin might translocate from the bowel into the blood stream in HF. Endotoxin may trigger immune activation in patients developed edema due to HF [27]. Continuous renal replacement therapy (CRRT) can reduce circulating cytokines and inflammatory mediators that result in ameliorating the central and peripheral manifestations of CHF [29]. CRRT after cardiac operations in children and adult could not only remove the fluid overload but also eliminate inflammatory mediators. It has been shown to improve hemodynamics, hemostatic dysfunction, pulmonary functions, and clinical outcome such as early morbidity [30–32]. CRRT is also effective in reducing BNP and circulating cytokines levels including IL-8 and monocyte chemoattractant protein-1 (MCP-1), as well as help patients regaining responsiveness to LDs in in a very small advanced HF population (5 patients) [33].

Although theoretically UF specific filter membrane could only penetrate small molecules such as sodium and water, there is no previous evidence from clinical studies on whether UF could filter out inflammatory mediators. It is not exactly certain whether UF is able to remove inflammatory mediators. Previous research found that high-volume continuous veno-venous hemofiltration combined with periodic filter change, different UF rates, different membrane pore sizes, different types of membrane, and different species were all related to the efficacy of removing inflammatory mediators by hemofiltration [34–36]. The capacity of filtering out mediators by UF specific filter membrane is influenced by many factors, such as pore size, screening coefficient of the membrane, molecular charge and molecular weight of the mediators. It is difficult to determine whether they can be filtered out only by the molecular weight of the mediators alone. Therefore, we will measure changes of serum and ultrafiltrate concentrations of inflammatory mediators including endotoxin, endothelin-1 (ET-1), tumor necrosis factor- (TNF-a), interleukin-6 (IL-6) and IL-10 in our study. We try to find out whether UF could relieve both fluid overload and other clinical manifestations such as HF related multiple organ dysfunction syndrome (MODS) in acute HF by filtering out certain inflammation mediators. Our study will provide further data regarding the ability of UF to filter out inflammation mediators. To our knowledge, this is the first trial exploring the effects of UF on circulating inflammatory mediators.

The present study is mainly limited by its open-label design and patient selection bias cannot be excluded, which will make the interpretation of the results somewhat limited. Also, the follow-up period is relatively short in our trial. Postpone the last clinical evaluation at 90 days and at an even later time point may provide more information of the advantages or disadvantages of UF.

In conclusions, this study evaluates the effectiveness and safety of selecting patients who are suitable and could benefit from early UF by certain risk factors to guide early UF treatment. Our research will provide clinical evidence for early UF in Chinese patients with acute decompensated HF and may contribute to volume overload reduction and clinical outcome improvement in this population. It also can help to prevent delay by clinicians to implement UF in the current domestic clinical practice of low rate of UF.

## Data Availability

Not applicable, the data has not been collected yet.

## List of Abbreviations

APTT: Activated partial thromboplastin time
CRRT: Continuous renal replacement therapy
eGFR: Estimated glomerular filtration rate
ET-1: Endothelin-1
HF: Heart failure
IL-6: interleukin-6
IV: Intravenous
LDs: Loop diuretics
MCP-1: Monocyte chemoattractant protein-1
MDRD: Modification of diet in renal disease
MLWHFQ: Minnesota living with heart failure questionnaire
MODS: Multiple organ dysfunction syndrome
NT-proBNP: N-terminal pro B-type natriuretic peptide
RRT: Renal replacement therapy
TNF-a: Tumor necrosis factor- a
UF: Ultrafiltration
